### Recruitment {15}

Shared accommodations are selected where there is a balanced resident structure in terms of country of origin, age, gender distribution, and family situation. Attention is also paid to the inclusion of different sizes and forms of housing (e.g., system construction, existing buildings, etc.). The sample will be drawn using the respondent driven sampling (RDS) method, a further development of snowball sampling, and like this is suitable for populations that are hard to reach [7, 30, 35, 36] for the researchers but whose members are well networked and enables weighting in the analysis through better control of the recruitment channels in order to ensure representativeness of the sample. Participants are invited to take part in the trial by the organizational support groups and with multilingual information material (the following languages are available: Arabic, Turkish, Farsi, Ukrainian, Russian, French, German, and English). During the conduct of the trial, the organizational support groups will make sure that participants continue in the trial by regularly reminding them to participate.

## Assignment of interventions: allocation

### Sequence generation {16a}

The sequence generation for this study's stepped-wedge design will be conducted considering ethics and practical feasibility. The order of interventions will be generated using a web-based random allocation method (random.org) to minimize biases and ensure fair distribution of the intervention across the clusters and its shared accommodations. This sequence generation will be performed by a member of the University Witten/Herdecke who will not be part of the data collection and analysis process to ensure appropriate randomization. Each of the nine shared accommodations will be randomized into one of the three clusters. Afterwards, the three clusters will be randomized to the three sequences according to the stepped-wedge design, which determines the point in time of the intervention.

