## Methods: participants, interventions, and outcomes

### Study setting {9}

The study will take place in nine shared accommodations in Stuttgart, Germany. The survey will consist of three clusters with three accommodations each. Using the web-based randomizing program random.org, shared accommodations are randomly assigned to each cluster. Implementation takes place in cluster A in weeks 1–3, cluster B in weeks 4–6, and cluster C in weeks 7–9. This results in five survey times t_0_–t_4_ (see Table 1): baseline, after implementation in clusters A, B, and C as well as the follow-up. In the study, data is collected and evaluated both at the level of the refugees and at the level of the qualification of the setting (qualification of the professionals in the shared accommodation, structural conditions of the setting). Qualified social workers or psychologists perform the implementation of the prevention concept.

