### Outcomes {12}

The primary outcome is the increase of knowledge about substances, hazardous substance use, and induced health risks among refugees since baseline. This will be measured with the Drug and Drug Problems Perception Questionnaire (DDPPQ; [4] in an adapted version to test the efficacy of the prevention measures in providing health-related information creating a sum score for a continuous variable. Primary outcome will be measured at the study times t_0_–t_3_.

The following short-term secondary outcomes are assessed 9 weeks after the first implementation: health literacy measured with eHealth literacy scale (eHeals; (Norman et al. [24, 25]), attitudes towards substance use measured with an adapted version of the Substance Abuse Attitude Survey (SAAS; [8]), and the increase in knowledge of the workforce about substances, hazardous substance use, and health risks among refugees measured with an adapted version of the Drug and Drug Problems Perception Questionnaire (DDPPQ; [4]) related to the intervention.

In order to relate the outcomes directly to the intervention, the DDPPQ; [4] and the SAAS [8] were adapted to the intervention and the context of the concept implementation. As in other studies [9, 22], where the DDPPQ was also adapted to specific contexts, statements about the validity of the scales need to be tested in a context-specific way.

The following long-term secondary outcomes are assessed three months after first implementation: depression, anxiety, and stress measured with Depression Anxiety Stress Scale (DASS–21; [21]) and reduction of hazardous substance use measured with DSM-5 criteria of substance use disorder [5], Obsessive Compulsive Drug Use Scale-5 score (OCDUS-5; [13], 30-day prevalence of hazardous substance use, and a self-assessment of problematic substance use [33].

Control variables are socio-demographic data (e.g., age, gender, and nationality) and contextual factors (e.g., accommodation size).

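### No balancing on site size is described when nine deliberately dissimilar accommodations are drawn into three steps; stratifying the draw is a cheap safeguard with a modest expected gain

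*Protocol article*

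**What the plan says.** Study setting {9} fixes the numbers: "The survey will consist of three clusters with three accommodations each". Sequence generation {16a} describes two random stages using random.org. First, "Each of the nine shared accommodations will be randomized into one of the three clusters". Then, "Afterwards, the three clusters will be randomized to the three sequences according to the stepped-wedge design". Neither stage names a stratum, a matching factor or a balance criterion. Only the count of three sites per group is fixed.

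Recruitment {15} says of the sites: "Attention is also paid to the inclusion of different sizes and forms of housing". The same section also says: "Shared accommodations are selected where there is a balanced resident structure in terms of country of origin, age, gender distribution, and family situation". So residents are meant to be alike across sites, while size and building type are meant to differ. Outcomes {12} lists accommodation size as a control variable, and Statistical methods {20a} plans covariate adjustment. Sample size {14} allows unequal site sizes around a target of 28 participants per site. Participant timeline {13} and Concealment mechanism {16b} place allocation after baseline, so site sizes can be known before the draw.

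**The concern.** The step is the randomised unit of contrast, and only three sites make up each step. The authors chose sites that differ in size and regard size as relevant to the outcome, but the described draw does not use it. The second stage only decides which group goes first, so it cannot repair an uneven first stage.

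Every site is observed before and after its start, so stable differences between large and small sites largely cancel. What does not cancel is change over time that differs by size. If large sites happen to be concentrated in an early or a late step, such change is partly read as an intervention effect. A main effect for size does not absorb it. The Discussion also wants to study how long the concept has been in place, and the longest exposure comes only from the three sites in group A. Finally, if participant numbers follow site size, steps carry uneven information and some precision is lost.

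**Working it through.** **The plan's figures.** The plan gives no figure for imbalance. Its sample size is 9 × 28 = 252. The power behind 252 cannot be reproduced, because neither the SD nor the within-person correlation is stated: with SD 1, 80% power needs 34 per site at a correlation of 0.75 and 27 per site at 0.80. This does not bear on the present point.

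**Counting allocations.** Possible allocations: 9!/(3!)³ = 1,680. Positions of the three largest sites: C(9,3) = 84.
- One in each step: 3³ = 27, so 27/84 = 32%.
- At least two in the same step: 1 − 27/84 = 68%.
- All three in one step: 3/84 = 3.6%.
- One site of each size third in every step: (3!)³ = 216, and 216/1,680 = 12.9%.

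**Precision.** Inputs from the plan: four periods (t0–t3), ICC 0.01, mean 28 per site. Assumptions: SD 1, participants proportional to site size, within-person correlation r of 0.5 or 0.7. The plan gives the coefficient of variation as 10 participants; read as an SD of 10, it is 10/28 = 0.36. For site *i* with m participants, the covariance of the period means is V = ICC·J + [(1 − ICC)/m]·[r·J + (1 − r)·I], where J is the all-ones matrix and I the identity. The SE of the treatment effect comes from generalised least squares with period effects, computed for all 1,680 allocations and for the 216 balanced ones.

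| Site sizes | r | Mean SE, all → balanced | Worst SE, all → balanced |
|---|---|---|---|
| Mean 28, SD 10 | 0.5 | 0.0815 → 0.0810 | 0.0846 → 0.0819 (3%) |
| Mean 28, SD 10 | 0.7 | 0.0643 → 0.0639 | 0.0667 → 0.0646 (3%) |
| 14, 16, 18, 24, 28, 32, 38, 40, 42 | 0.5 | 0.0816 → 0.0810 | 0.0854 → 0.0815 (5%) |
| 14, 16, 18, 24, 28, 32, 38, 40, 42 | 0.7 | 0.0644 → 0.0639 | 0.0673 → 0.0643 (5%) |

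The mean gain is under 1% throughout. In a much more skewed set (CV 0.63, r = 0) the mean SE goes from 0.1081 to 0.1066 (1.4%) and the worst from 0.1174 to 0.1091 (7%). If every site recruits exactly 28, all allocations have the same SE and the precision gain is nil.

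**Size-dependent drift.** Assume that knowledge changes by an extra 0.02 SD per period for each SD of site size, and pass that through the same estimator.
- All draws, sizes 14–42, r 0.5–0.7: SD of the error about 0.0054–0.0060, worst draw 0.016–0.018 (about 11–12% of the planned difference of 0.15).
- Balanced draws: SD 0.0015–0.0017 for the bunched set in the table and 0.0023–0.0025 for sizes evenly spaced from 14 to 42. The worst draw is about 70–80% lower.
- Mean error over all 1,680 draws: 0.0001, essentially zero.
- Against the SE: 0.0060/0.0816 = 7% and 0.0054/0.0644 = 8%. In quadrature, √(1 + 0.08²) − 1 = 0.3% more total error.

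The error is proportional to the assumed drift. At 0.01 it halves (0.0027–0.0030). At 0.05 it is 2.5 times as large (0.0135–0.0150). Longer tails in the size distribution weaken the protection: in the SD 10 set the balanced error SD is about 0.003.

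**Housing form.** If four of the nine sites share a form (assumption), the chance that some step is uniform in form is (18 + 45 − 18)/126 = 36%. The terms are placements with one step all of the minority form, with one step holding none of it, and with both. Stratifying on size does not control this.

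**The case against.** A fixed three-three-three random draw by someone outside data collection and analysis is valid, and nothing in the protocol contradicts it. A reader might infer that the estimate is biased. It is not: the error averages to zero over draws, and in the illustration it is a small fraction of one SE. A reader might also infer that large sites will probably all land together. That happens in 3.6% of draws; the likely event is two of three. The drift is an assumption, since no section says that knowledge changes with accommodation size over roughly ten weeks. Size in the sense of residents need not track participants, given the target of 28 per site. Residents are selected to be similar across sites, size is a planned control variable, and each site is its own comparison. The article is condensed, so a constraint may stand elsewhere.

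Most of this stands, and it limits the size of the point. Two things remain. Item {16a} is where a constraint on the draw would be named, and the method it describes has none. And a size main effect does not deal with size-by-time change. It also stands that balancing on size leaves housing form alone and is not entirely free.

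**Conclusion.** The point holds as a low-cost improvement, not as an error. The described draw ignores a site characteristic that the authors deliberately varied and plan to adjust for, and some size imbalance is likely (68% for two of the three largest together). The consequence is modest: less than 1% in mean SE and about 3–5% in worst-draw SE, provided that participant numbers vary with site size at a CV near 0.36 to 0.38. The protection against size-dependent drift is real in relative terms, but its absolute size rests wholly on an assumed drift. The benefit is insurance against a bad draw. The documents do not support a claim that the trial is biased, that similar sites of every kind would be separated, or that the change costs nothing.

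**What to change.** In {16a}, state that the nine sites are ranked by size before the draw (with size defined once, for example as number of residents), grouped into three triplets, and that within each triplet one site is randomised to each of A, B and C. Include the size stratum in the model and add a size-by-period sensitivity model, because the stratum alone does not address drift.

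Cost: a sentence or two in the protocol, the same person and the same tool, and no extra participants or staff. Allocations fall from 1,680 to 216, which still supports a randomisation test at 5% (smallest possible p = 1/216 = 0.005). Site sizes must be fixed before the draw. Housing form remains unbalanced.

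Trial status gives version 2 as 08/2024 and recruitment from 06/2024, so the draw may already have been made. In that case, report size and housing form by step and run the size-by-period sensitivity model.

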### Concealment mechanism {16b}

Intervention allocation will be given to the research team after baseline. Therefore, researchers, workforce, and refugees responsible for implementing the interventions will only gain access to the relevant information after the sequence is determined.

### Implementation {16c}

The implementation of the prevention concept will be carried out by a multidisciplinary team of professionals, including researchers of the study team, social workers, and psychologists as well as refugees living in shared accommodations. Staff and peer training will be conducted beforehand to ensure consistent and standardized implementation. The implementation of the prevention concept is developed in close collaboration with residents of shared accommodations to ensure high acceptance and effectiveness.

## Assignment of interventions: blinding

### Who will be blinded {17a}

This is not applicable because blinding is not possible for this specific study.

### Procedure for unblinding if needed {17b}

Not applicable, see 17a.

## Data collection and management

### Plans for assessment and collection of outcomes {18a}

The trained research team is responsible for organizing and conducting the data assessment. Data will be assessed using a multilingual questionnaire containing different item blocks and psychometric scales. The multilingual questionnaire is based on the Measurements in the Addictions for Triage and Evaluation Questionnaire (MATE-Q; [32, 33] and supplemented with other scales and items to measure primary and secondary outcomes. MATE-Q was chosen because of its validity [26], its availability in different languages (e.g., Farsi, Arabic, Turkish, French and Russian), and the possibility of its easy self-completion [33]. It contains questions about substance use and gambling, 30-day prevalence, andlifetime prevalence, the Obsessive Compulsive Drug Use Scale-5 (OCDUS-5; [13]), and items aligned with the DSM-5 substance use disorder criteria [5]. Further on, MATE-Q asks for information about mental and physical well-being, distress, comorbid mental disorders, and ICF-related items addressing problems with relationships and basic requirements. It also contains the Depression Anxiety Stress Scale (DASS–21; [21]).

Further scales not included in the MATE-Q were supplemented. These supplemented scales are a migration-sensitive version of the MacArthur scale [3] based on Schumann et al. [34] to measure subjective social status and the eHealth Literacy Scale (eHeals, [24]) to assess health literacy regarding health information on the Internet. The questionnaire was further enhanced with self-created items to assess sociodemographic and contextual factors as well as with an adapted version of the Drug and Drug Problems Perception Questionnaire (DDPPQ [4, 22]), to measure the knowledge about substance use, an adapted version of the Substance Abuse Attitude Survey (SAAS; [8]), and questions about the satisfaction regarding the living situation based on the German Socio-Economic Panel study (TNS Infratest Sozialforschung, [37]). Participants can gain access to the questionnaire via QR codes for each language (Arabic, Turkish, Farsi, Russian, French, German, and English).

### Plans to promote participant retention and complete follow-up {18b}

Participants will be motivated to participate and to continue participation in the study during the data collection period by incentives (gift cards) and by reminders from the research team and are encouraged by the workforce on site to reduce drop-out and to minimize missing data.

### Data management {19}

Data management will be performed at University of Applied Sciences Esslingen. Data will be collected using EvaSys (data software) and analyzed using R [29].

### Confidentiality {27}

Personal information about the participants will be stored securely at University Esslingen and will be accessible only for the research team. Participants’ data from the questionnaire and the documents that contain the name and signature of the participants will be stored separately. In the run-up to the study, the research team worked closely with the data protection officer and developed a data protection concept. In particular, procedures were developed for the confidentiality of stored data and documents as well as the handling of personal and personally identifiable data. The data protection concept created implements all regulations stipulated by the EU General Data Protection Regulation (EU GDPR) and the Baden-Württemberg State Data Protection Act (LDSG BW, new). Only accumulated and anonymized data will be available for publication after the trial.

### Plans for collection, laboratory evaluation, and storage of biological specimens for genetic or molecular analysis in this trial/future use {33}

This is not applicable because no biological specimens will be collected in this trial.

## Statistical methods

### Statistical methods for primary and secondary outcomes {20a}

For the primary outcome, multilevel linear regression analyses will be employed. The variation of the effect by cluster and over time will be examined [10]. For secondary short- and long-term outcomes, depending on the variable, both multilevel linear and multilevel logistic regression analyses will be used. These methods are suitable for analyzing clustered data, which is inherent in the stepped-wedge design used in this study. Multilevel modeling allows for the examination of individual-level and cluster-level effects, capturing the hierarchical structure of the data. Regression models will be adjusted for relevant covariates to account for potential confounding factors.

### Interim analyses {21b}

Not applicable. As Table 1 shows, the trial duration is very short. Due to the stepped-wedge methodology and the phased implementation in the different clusters, interim analyses are not planned. As this was considered to be a low-risk intervention, no formal stopping rules are implemented. However, as explained in item 22, the occurrence of serious adverse events is recorded and discussed in the trial steering committee, which would be able to stop the trial if necessary.

### Methods for additional analyses (e.g., subgroup analyses) {20b}

Additional analyses, such as subgroup analyses, will be conducted to explore potential effect modifiers and assess intervention effectiveness across different subpopulations. Subgroup analyses will involve stratifying the sample based on relevant demographic and clinical characteristics. Interaction terms will be included in the regression models to test for effect modification. Subgroup-specific estimates will be reported, allowing for a comprehensive understanding of intervention effects within specific subgroups. Furthermore, predictors for hazardous substance use will be examined using multilevel logistic regression.

### Methods in analysis to handle protocol non-adherence and any statistical methods to handle missing data {20c}

To address protocol non-adherence, an intention-to-treat analysis approach will be employed, where participants are analyzed according to their randomized group assignment, regardless of the intervention received. Additionally, per-protocol analyses will be conducted to assess the robustness of the findings. In handling missing data, multiple imputation [6] will be utilized if necessary. Multiple imputation accounts for the uncertainty associated with missing data by creating multiple plausible imputed datasets. These datasets are analyzed separately, and the results are combined using appropriate rules to provide valid statistical inference. Sensitivity analyses will be conducted to assess the impact of missing data assumptions on the study findings.

### Plans to give access to the full protocol, participant-level data, and statistical code {31c}

This is not applicable because considering sensible topics (trauma, substance use), there are no plans to give full access to the full dataset.

## Oversight and monitoring

### Composition of the coordinating center and trial steering committee {5d}

To conduct and support the trial, different groups are involved in the research project:The *project management group* at the coordinating center is the research team of Esslingen University of Applied Sciences, consisting of the PI, investigators, and research assistants. The coordinating center is responsible for project management and will meet once a week for the duration of the trial to review the trial conduct. Additional meetings will be held in case of the reporting of serious adverse events.The *trial steering committee* has the strategic control about the project and is composed of the researchers in the coordination center, psychologists, social workers, and refugees and also includes public stakeholders from local social welfare and the public health department. The trial steering committee will meet at the start and at the end of the trial. Additionally, meetings will be held on invitation of the project management group in case of serious adverse events and/or challenges to the trial conduct during the course of the trial.The *organizational support groups* are involved in running the trial day-to-day and provide organizational support on each of the nine trial sites. These groups are composed of the staff (social workers and psychologists) in the shared accommodations.The *scientific advisory board* consists of researchers from other universities, politicians and decision-makers from health care sector on national level, experts for substance use prevention on national and federal level, a representative of the social welfare office on a municipal level, and refugees from refugees’ self-organizations. The scientific advisory has met in advance in the planning phase of the trial and discussed the study design and ethical aspects. Additionally, it will be consulted by decision of the trial steering committee in case of challenges in the trial conduct and/or serious adverse events.

### Composition of the data monitoring committee, its role and reporting structure {21a}

This is not applicable because there is no data monitoring committee.

### Adverse event reporting and harms {22}

The overriding principle of the research project is to exclude or minimize the risks for the refugees participating in the surveys. For this reason, there is a close cooperation with the social workers on site of the shared accommodations and their management to provide assistance plans and help services for unforeseen events during the survey (counselling services, educational and psychological support, etc.). In addition, a psychological background service is installed and will be available to deal with psychosocial crises and trauma-related disorders that occur during the data collection. This psychological background service is led by a psychologist and psychotherapist who has a special qualification in dealing with mental health crises.

Possible adverse events among refugees might be the occurrence of clinically relevant problems (e.g., flashbacks in the context of a trauma disorder, or suicidal tendencies). In this case, the local support system will be activated, and, if necessary, the background service will be contacted, or other support systems (e.g., psychiatric emergency services) will be activated.

Furthermore, refugees might experience stress caused by the perceived similarity of the survey process to official appointments as part of their asylum process. That is why providing information about the trial, how to participate, and the fact that it will not have anything to do with asylum decisions is very important. Therefore, information material will be provided in different languages (see above).

It is assumed that the risks for the workforce participating in the study are no higher than corresponding situations that occur in everyday professional life. However, if there are indications of severe stress, advice is given on site; in the event of exceptionally high stress, the background service is consulted.

Any risks that arise are documented by the researchers on site or by the organizational support groups on a standard form and immediately made available to the project management group at the coordinating center and to the trial steering committee. This standard form was developed in advance as part of the ethical clearing process. After this ethical clearing process, the Alice Salomon University Ethics Committee in Berlin (file reference: 01–2024/62) provided ethical approval for this study and considered the intervention as low risk.

In the event of serious adverse events, the project management group decides on the next steps. Indicators of exceptionally high stress (such as panic attacks, suicide attempts, or completed suicides) are reported directly to the members of the steering committee by the project management group. In the event of trial-related serious adverse events, the trial steering committee decides whether to discontinue the study. In that case, the scientific advisory board will also be conducted. The criterion for discontinuing the study is defined as an unreasonable burden on the participants as determined by the trial steering committee. This is decided by a majority vote at an extraordinary meeting on the basis of the available risk documentation. The convening of the extraordinary meeting of the steering committee is convened by the project lead.

